### Participant timeline

In-patients and out-patients will regularly be screened for participation eligibility. If the eligibility criteria are met and in consultation with their treating clinicians, patients will be informed about their study and will have at least one day to consider participation and sign the informed consent. The same procedure applies for clinicians who participate in the study, while they only must consent once for the recording of therapy sessions with several patients who gave informed consent. From the time point on where patients agreed to participate, up to five of their regularly held therapy sessions will be recorded. After the therapy session, patients and therapists will fill out questionnaires about the psychopathology of the patient (approx. 5 min. for each). They are asked to fill out the questionnaire on the same day the therapy session took place. Table 1 summarizes the procedure and when the respective questionnaires are used.

**Table 1 T1:** Content for the schedule of enrollment and participation.

TIMEPOINT	Enrollment	Informed Consent	Recording and Questionnaires				
	*−t2*	*−t1*	*t1*	*t2*	*t3*	*t4*	*t5*
	Ongoing	After confirmation by clinician	At least 1 week between each participation				
			Up to five therapy sessions can be recorded per participant				
			Questionnaires have to be filled out the same day as the recording				
*Study admission*							
Eligibility screen	X	X					
Consultation with the treating clinician	X						
Informed consent		X					
*Recording of therapy session*			X	X	X	X	X
*Patient reported outcomes (PRO)*							
*Beck’s Depression Inventory (BDI-II)*			X	X	X	X	X
*DSI-SS-Scale*			X	X	X	X	X
MINI C Suicidality Scale			X				
*Demographics, Diagnoses and Concomitant Medication*			X				
*Therapist Ratings*							
*Global Assessment of Functioning (GAF)*			X	X	X	X	X
*Clinical Global Impression (CGI)*			X	X	X	X	X
*Brief Psychiatric Rating Scale (BPRS)*			X	X	X	X	X

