### Sample size

To determine the required sample size for comparing the accuracy of our models against the gold standard of a trained psychiatrist's evaluation, we conducted an *a priori* power analysis using G*Power software (43).

We based our effect size estimate on the accuracies reported in previous studies that used machine learning techniques to predict suicidality from clinical data (44). Pestian et al. (45) reported an accuracy of 85%, Bernert et al. (46) reported 90% among 87 studies in their meta-analysis, and Barak-Corren et al. (47) reported 94%. The average accuracy across these studies is 89.2%. Assuming a gold standard accuracy of 100%, we calculated an effect size (Cohen's g) of 0.11 using the formula: g = (P—Po)/√[Po(1—Po)], where *P* is the expected accuracy (0.892) and Po is the gold standard accuracy (1.0).

For our power analysis, we set the following parameters: a two-tailed test, an alpha level of 0.05, a power of 0.80, and a constant proportion of 0.5 (representing a balanced dataset). The results indicated that a total sample size of 162 is required to detect an effect size of 0.11 with 80% power at a significance level of 0.05. The critical values for the lower and upper bounds of the acceptance region are 68 and 94, respectively. The actual power achieved with this sample size is 0.8046757, and the actual alpha level is 0.0491726.

In summary, to compare the accuracy of our models against the gold standard of a trained psychiatrist's evaluation with 80% power and a 5% significance level, we require a total sample size of *n* = 162, assuming an effect size of 0.11 based on the accuracies reported in previous comparable studies. As we expect a drop-out rate of 15%–20% due to technical issues, quality issues etc., we expect to collect *n* = 200 interviews.

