Tier 1: Unimodal Baseline Analysis. We will analyze each modality independently to establish baseline predictive performance before considering fusion. For the text modality, we will conduct two-way mixed-effects logistic regression with outcomes (diagnostic classification or severity degree) regressed on the fixed effects of model size and temperature, with random intercepts for participant and session. Effect sizes will be reported as odds ratios with 95% confidence intervals. For the acoustic modality, we will conduct mixed-effects linear regression using a reduced set of the most clinically relevant acoustic features selected *a priori* based on prior literature associations with depression and suicidality, including pitch variability, energy measures, MFCC and jitter as predictors of continuously scored clinical outcomes (e.g., severity scores from standardized rating scales) (60, 61).Tier 2: Factorial Interaction Analysis for 2 × 2 Design. For text-based predictions, we will formally test the 2 × 2 factorial design using mixed-effects ANOVA to partition variance according to main effects (model size, temperature) and their interaction. Specifically, we will model primary outcome (e.g., predicted depression severity) as a function of fixed effects for model size (GPT-OSS-120B vs. 20B), temperature (0.1 vs. 0.8), and their interaction (Model Size × Temperature), with random intercepts for participants and sessions to account for the hierarchical data structure. This approach allows us to determine whether inference strategy recommendations (conservative vs. liberal temperature) can be applied consistently across model sizes, or whether optimization differs by model choice. If a significant Model Size × Temperature interaction emerges, it would suggest that clinical deployment requires model-specific tuning. Conversely, absence of interaction would support unified recommendations applicable regardless of computational constraints. We will report partial eta-squared (*η*²p) effect sizes with 95% confidence intervals for each factorial term.Tier 3: Multimodal fusion and Late-Fusion Integration. To evaluate how textual and acoustic information combine for clinical prediction, we will employ a structured late-fusion approach. For each of the four 2 × 2 factorial conditions, we will generate separate predictions from the GPT-OSS models (text modality) and from a logistic regression model trained on acoustic features (acoustic modality). We will then integrate these predictions through weighted averaging, with weights determined via cross-validation (80% training, 20% held-out validation) on a stratified subset of sessions. This approach maintains interpretability—each modality's contribution can be quantified—and avoids the architectural complexity that would introduce uncontrolled hyperparameter flexibility incompatible with pre-registration.We will quantify multimodal benefit by comparing fusion performance (AUC, sensitivity/specificity at clinically relevant decision thresholds) against the best unimodal baseline. If fusion provides incremental improvement beyond single modalities, we will use mixed-effects logistic regression with interaction terms to test whether the fusion benefit depends on model size or temperature setting. This tests the hypothesis that acoustic information provides complementary information that enhances text-based predictions uniformly, or whether certain model configurations better leverage multimodal information.

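### The 80% power assumes 162 independent observations, but the counted unit is the interview and one patient may supply up to five

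*Protocol article*

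**What the plan says.** The Sample size section sets "a two-tailed test, an alpha level of 0.05, a power of 0.80" and "a constant proportion of 0.5 (representing a balanced dataset"), and concludes that "a total sample size of 162 is required to detect an effect size of 0.11 with 80% power at a significance level of 0.05". It adds: "The critical values for the lower and upper bounds of the acceptance region are 68 and 94, respectively". It also reports: "The actual power achieved with this sample size is 0.8046757, and the actual alpha level is 0.0491726". The 162 is then raised to 200 for an expected loss of 15% to 20% from technical and quality problems. The thing counted at that step is the interview, not the patient.

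Under Participant timeline, once a patient has consented, "up to five of their regularly held therapy sessions will be recorded". Table 1 shows the same five time points, at least a week apart. Clinicians may be recorded with more than one patient: "they only must consent once for the recording of therapy sessions with several patients who gave informed consent".

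Under Statistical methods for primary and secondary outcomes, the Tier 1 text models are fitted "with random intercepts for participant and session". Tier 2 repeats these intercepts and gives the hierarchical structure of the data as the reason.

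The Sample size section gives no number of patients, no expected mean number of sessions per patient, no within-patient correlation and no design effect.

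**The concern.** The binomial calculation is valid only if the 162 results are independent. Two sessions of one patient share the same illness, voice and way of speaking, so a model that is right or wrong about one session will tend to be right or wrong about the next. The analysis section accepts this dependence and the sample size section does not. The two parts of the article therefore rest on different assumptions about the same data.

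Two things are at stake. If the analysis allows for clustering, the information in 162 interviews is less than the calculation assumes, and so is the power. If a session-level test or interval ignores clustering, its error rate exceeds the nominal 5% and its interval is too narrow. The second risk is live because the t-tests or agreement coefficients under Outcomes, and the AUC and sensitivity/specificity in Tier 3, come with no stated allowance for repeated sessions.

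**Working it through.** **1. The plan's own figure.** Inputs from the Sample size section: null proportion 0.5, g = 0.11 (so the alternative is 0.5 + 0.11 = 0.61), n = 162, reject if the count is 68 or fewer or 94 or more.
- Alpha = P(X ≤ 68) + P(X ≥ 94) for X ~ Bin(162, 0.5) = 0.0491726.
- Power = the same two tails for X ~ Bin(162, 0.61) = 0.8046757.

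Both match the printed values to every digit. The calculation is therefore an exact binomial test on 162 independent units. Among nearby sizes, n = 160, 161 and 163 give 79.6%, 77.7% and 78.6%, so 162 has almost no slack.

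**2. The reserve.** 162/0.85 = 191 and 162/0.80 = 203. Conversely, 200 × 0.80 = 160 and 200 × 0.85 = 170. The technical loss alone uses up the 200 interviews, and nothing is left for a design effect.

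**3. Allowing for clustering.** The article gives neither m, the mean sessions per patient, nor the ICC, meaning here the correlation between two sessions of one patient in whether the model's result is correct. (This is not the agreement coefficient named under Outcomes.) Both are assumptions below.
- Design effect DE = 1 + (m − 1) × ICC; effective n = 162/DE.
- Power of a clustering-adjusted test, normal approximation: Φ[(0.11 × √(effective n) − 1.96 × 0.5) / √(0.61 × 0.39)]. At n = 162 this gives 80.5%, in line with the exact value.
- Type I error of an unadjusted test: 2 × [1 − Φ(1.96/√DE)].
- Power of the unadjusted 68/94 rule: beta-binomial simulation, 40,000 runs.

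| m | ICC | DE | Effective n | Adjusted test: power | Unadjusted test: type I error | Unadjusted test: power |
|---|---|---|---|---|---|---|
| 2 | 0.1 | 1.1 | 147 | 77% | 6% | 80% |
| 2 | 0.3 | 1.3 | 125 | 69% | 9% | 78% |
| 2 | 0.5 | 1.5 | 108 | 63% | 11% | 76% |
| 3 | 0.1 | 1.2 | 135 | 73% | 7% | 78% |
| 3 | 0.3 | 1.6 | 101 | 60% | 12% | 75% |
| 3 | 0.5 | 2.0 | 81 | 51% | 17% | 73% |
| 5 | 0.1 | 1.4 | 116 | 66% | 10% | 77% |
| 5 | 0.3 | 2.2 | 74 | 47% | 19% | 72% |
| 5 | 0.5 | 3.0 | 54 | 36% | 26% | 70% |

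The adjusted and unadjusted columns are alternatives; a given test suffers one problem or the other. Simulated type I error under the 68/94 rule agrees with the formula (for example 12.3% at m = 3, ICC 0.3, and 18.3% at m = 5, ICC 0.3). Even at m = 2 and ICC 0.05 the adjusted power is 78.6%.

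The normal approximation is used because an exact binomial at a rounded effective n attains less than 5% alpha and so understates power. At n = 116, for instance, attained alpha is 0.032 and power 60%, against 66% by the approximation.

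**The case against.** **Five sessions is a maximum.** Participation ends when treatment ends, and sessions are at least a week apart, so the mean may be well below five. A reader might infer that power is near 40%, or that only 200/5 = 40 patients will be studied. The article supports neither; those are the extreme end of the range. The point stands because power is below 80% even with two sessions per patient and a small correlation.

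**The arithmetic is right.** It is, to seven decimals. A reader might call this a calculation error, but the fault is an independence assumption that the design does not support.

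**The expected accuracy is 89.2%, not 61%.** At 0.892 against 0.5, power would exceed 99.9% even at an effective n of 54. That is true, but the article's 80% is claimed at g = 0.11, which its own critical values show to be 61% against 50%. How 0.11 was derived is a separate question. Nothing here shows that the study could not detect an accuracy of 89.2%.

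**Model size and temperature are compared within the same sessions.** Patient effects partly cancel in those contrasts, so the design effect above does not carry over to them directly. This stands and limits the point to the powered accuracy comparison and to session-level intervals.

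**Mixed models are already planned.** They protect the inference where they are used, but they do not restore the power.

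**Therapists.** A reader might infer that leaving out a therapist term makes the standard errors too small. The powered comparison uses an independent psychiatrist's rating (Data management), so the claim does not reach it. For severity rated by the treating therapist, the effect depends on how many therapists there are and on whether acoustic features also cluster by therapist; neither is given. The participant intercept may also absorb part of it.

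**Conclusion.** The concern holds as an unsupported independence assumption in the sample size. The 80% printed for g = 0.11 is not delivered by 162 interviews unless nearly every patient gives one session or the within-patient correlation is about zero, and the article plans for neither.

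The size cannot be fixed from the document. Over assumed correlations of 0.1 to 0.5, clustering-adjusted power runs from about 77% down to 63% for two sessions per patient, 73% to 51% for three, and 66% to 36% at the ceiling of five. If clustering is ignored instead, type I error runs from about 6% to 26% over the same grid. These figures rest on equal numbers of sessions per patient and on the plan's own effect size.

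**What to change.** 1. In the Sample size section, state the planned number of patients and the expected mean sessions per patient, alongside the number of interviews.
2. Restate power, or the expected confidence interval width, with effective n = 162/(1 + (m − 1) × ICC) over a stated range of ICC.
3. Compute intervals for accuracy, sensitivity/specificity and AUC, and the t-test or agreement analyses under Outcomes, with a participant-level cluster bootstrap or a mixed model.
4. For diagnostic classification, count patients as the unit. Table 1 collects the diagnosis once, at t1, so further sessions add no new label.
5. Optionally, add a therapist random intercept as a sensitivity analysis for models of therapist-rated severity (GAF, CGI, BPRS). Its variance may be imprecise if therapists are few.

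The cost is mainly wording and a change in how intervals are computed, with no extra enrolment. The stated power falls and the intervals widen. Restoring 80% would be a different decision. At ICC 0.3 with 20% loss it would take 162 × 1.6/0.80 = 324 interviews at three sessions per patient, or 162 × 2.2/0.80 = 446 at five, against the 200 planned.

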**Discussion:**

During the implementation of our research project, we were faced with challenges regarding the security of patient privacy and the technical implementation of therapy recordings toreassure sufficient data quality for the data analysis. Therefore, in addition to improve the suicidality prediction with multimodal methods we will develop an end-to-end-workflow for further AI-research in the clinical context.

**Clinical Trial Registration**: https://drks.de/search/de/trial/DRKS00027878, identifier DRKS00027878.

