### Data management

During the data collection phase, the raw audio recordings, patient data, and questionnaires will be collected. In this phase, only clinicians and student assistants from the University hospital in Frankfurt as well as one doctoral student from the Privatklinik [name] in Königstein are involved. The analysis of the data is conducted by the Ubiquitous Knowledge Processing (UKP) Lab at TU Darmstadt using natural language processing and multimodal methods and is mostly carried out in Darmstadt exclusively with pseudonymized data. The data accessed by the research group from TU Darmstadt will only have pseudonymized files and data without any personal information about the participants. The data analysis is complemented by a standardized assessment of the course by an independent board-certified psychiatrist or experienced assistant in psychiatry, serving as a “gold standard” for comparison with the AI analysis. Thus, the pseudonymized audio files are listened to and classified by a board-certified psychiatrist based on clinical features. The gold standard assessment covers three different areas. It consists of the BPRS as a broad psychopathology questionnaire, the five-stage severity item of the CGI-SS combined with an open question, asking the experts to briefly justify their rating within 2–3 sentences and the VTAS-R-Short Form, a five-item therapeutic alliance questionnaire (55).

The pseudonymized audio recordings will then be analyzed for acoustic and prosodic features using the open-source toolkit, openSMILE (56) and then transcribed to text with the freely available software WhisperX (57). Both datasets will then be analyzed on its own and later on fed to a multimodal neural network to generate a clinically relevant outcome score (e.g., suicidality prognosis score). Figure 1 shows an overview of our workflow.

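### The 80% power at n = 162 covers only models scored on all 162 interviews; the plan does not say on how many sessions the fitted acoustic and fused models are assessed

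*Protocol article*

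**What the plan says.** The Sample size section sets the test as "a two-tailed test, an alpha level of 0.05, a power of 0.80, and a constant proportion of 0.5 (representing a balanced dataset"). It reports that "a total sample size of 162 is required to detect an effect size of 0.11 with 80% power at a significance level of 0.05". It adds: "The critical values for the lower and upper bounds of the acceptance region are 68 and 94, respectively". It also states: "The actual power achieved with this sample size is 0.8046757, and the actual alpha level is 0.0491726". The closing summary applies the result to the study's models as a group ("with 80% power and a 5% significance level, we require a total sample size of" 162). The target is then raised to 200 interviews for an expected 15% to 20% loss from technical and quality problems. No other allowance is made.

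The section Statistical methods for primary and secondary outcomes describes three kinds of model:

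- **Text:** GPT-OSS models used zero-shot, so nothing is fitted to study data.
- **Acoustic (Tier 3):** a logistic regression fitted to acoustic features. Its training share is not stated.
- **Fused (Tier 3):** a weighted average of the other two, "with weights determined via cross-validation (80% training, 20% held-out validation) on a stratified subset of sessions".

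Tier 3 then compares fusion with the better single modality on AUC, sensitivity and specificity, without naming the sessions used. The Data management section says both datasets are "later on fed to a multimodal neural network to generate a clinically relevant outcome score". The abstract states the aim as "in addition to improve the suicidality prediction with multimodal methods".

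**The concern.** A power statement for a group of models is valid for each of them only if each is scored on the assumed number of interviews. The text models can be scored on every usable interview. A model fitted to study data can be assessed fairly only on sessions that did not contribute to the fit. The plan has at least one such model and a set of fitted weights, but its sample size treats all models alike.

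The Tier 3 wording can be read as one 80/20 split, possibly within only part of the data. In that case the fused model, and perhaps the acoustic one, would be judged on about a fifth of the interviews or fewer. Tier 3 tests whether the fusion benefit depends on model size or temperature only if fusion first shows an improvement. An imprecise first result would therefore decide what is analysed next.

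**Working it through.** **Inputs.** Two-sided alpha 0.05, null proportion 0.5, effect size g = 0.11 (alternative 0.5 + 0.11 = 0.61), n = 162, 200 interviews collected and 15% to 20% loss, all from Sample size. The 80/20 proportion is from Tier 3. My assumptions are equal numbers of positive and negative sessions, and sessions treated as independent.

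**Step 1: reproduce the plan's figure.** Use the exact binomial test with at most 0.025 per tail under p = 0.5. Power is P(X ≤ lower) + P(X ≥ upper) under p = 0.61. At n = 162 the critical values are 68 and 94, alpha is 0.0491726 and power is 0.8046757. All match, and 162 is the first n to reach 80%.

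**Step 2: size of a single 20% hold-out.**

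- 0.20 × 162 = 32.4, so about 32.
- Usable interviews: 200 × 0.80 = 160 to 200 × 0.85 = 170, so 32 to 34 held out.
- With no losses: 0.20 × 200 = 40.

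**Step 3: the same routine at those sizes.**

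| Sessions scored | Critical values | Actual alpha | Power |
|---|---|---|---|
| 162 | 68 / 94 | 0.049 | 0.805 |
| 32 | 9 / 23 | 0.020 | 0.140 |
| 33 | 10 / 23 | 0.035 | 0.200 |
| 34 | 10 / 24 | 0.024 | 0.166 |
| 40 | 13 / 27 | 0.038 | 0.251 |

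The test is discrete, so power does not rise smoothly with n. The normal approximation, Φ[(0.11 − 1.96√(0.25/n)) / √(0.61 × 0.39/n)], gives 0.23 at n = 32 and 0.28 at n = 40. To leave 162 interviews in a single 20% hold-out would take 162 / 0.20 = 810 interviews.

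**Step 4: precision, which does not depend on that routine.** The Hanley–McNeil variance for AUC A with m positives and m negatives is [A(1 − A) + (m − 1)(Q₁ − A²) + (m − 1)(Q₂ − A²)] / m², where Q₁ = A/(2 − A) and Q₂ = 2A²/(1 + A). With A = 0.85, Q₁ = 0.7391, Q₂ = 0.7811 and A² = 0.7225.

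- m = 16 (n = 32): (0.1275 + 15 × 0.0166 + 15 × 0.0586) / 256 = 0.0049. SE 0.070, 95% half-width 1.96 × 0.070 = 0.14.
- m = 81 (n = 162): (0.1275 + 80 × 0.0166 + 80 × 0.0586) / 6561 = 0.00094. SE 0.031, half-width 0.06.

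For sensitivity, the exact 95% interval is 54% to 96% for 13/16, against 73% to 90% for 67/81.

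**Step 5: the rotating reading.** With five folds over all sessions, each interview is held out once. All 162 receive an out-of-fold prediction, and nominal power stays at 0.805 if dependence between folds is ignored.

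**The case against.** The strongest reply is that Tier 3 says cross-validation. In ordinary use an 80/20 cross-validation is five-fold, and then nothing is lost. That may be what was meant. The text, however, gives one proportion, calls the 20% held-out validation and confines it to a subset of sessions. It never says that every session gets an out-of-fold prediction.

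Several further points stand and limit the claim:

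- The split is attached to the fusion weights only. A reader might infer that the acoustic model is also trained on 80% of all interviews, but the plan does not say so.
- The subset works in more than one direction. A smaller subset means a smaller hold-out, yet sessions outside it could form a larger test set. Conversely, if the 20% is itself used to choose the weights, it is not a clean test set for fusion.
- A reader might conclude that the multimodal analysis has 14% power. It does not follow. The routine tests 0.61 against 0.5, not fusion against a single modality. With the plan's expected accuracy of 0.892 against 0.5, the same test at n = 32 has power 0.9985. Also, 14% is a low point of the discrete test.
- No power was computed for the paired fusion difference, so one cannot say that a real benefit would probably be missed. The intervals above are for single models. A paired difference would be narrower if the predictions correlate.
- The plan names the comparison of the two zero-shot text models as its primary analytical comparison, and sizing a study on that is normal.

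Details of the evaluation set could be left to a fuller document. But this article does fix a split on a subset, and does state the power for its models without distinction. Those two statements need to be reconciled.

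**Conclusion.** The point holds in a conditional form. The 162 interviews and 80% power are correctly computed, but they apply only to models scored on all 162 interviews. As written, they are claimed for fitted models as well, with no allowance for fitting and no stated evaluation set.

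If a single 20% hold-out is meant and fusion is assessed on it, about 32 to 40 sessions remain. The plan's routine then gives about 14% to 25%, and the single-model AUC half-width at n = 32 is about 0.14 instead of 0.06. If five rotating folds over all sessions are meant, nominal power is unchanged and only the wording needs repair. These figures assume balanced classes and independent sessions. They do not show that the fusion comparison itself is underpowered by any particular amount.

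**What to change.** In Tier 3, replace the 80/20 split on a subset with five-fold cross-validation over all usable sessions. Keep all of a participant's sessions (up to five) in the same fold, so that no patient is on both sides of a split. Fit both the acoustic model and the fusion weights inside the training folds. Compute text, acoustic and fused metrics on the pooled out-of-fold predictions, so that all three are compared on the same sessions.

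In Sample size, state that 162 and 80% apply to models scored on all 162 interviews. If a single hold-out is kept, state its number of sessions and the expected precision of AUC, sensitivity and specificity. If rotating folds were already intended, it is enough to say so, replace the reference to a subset with all usable sessions, and state the grouping by participant.

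The cost is a few extra model fits and some wording. No further patients or data are needed.
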